## Methods

The protocols of prospective repeated-measurement studies from which participants will be recruited for this longitudinal investigation are registered online (ClinicalTrials.gov Identifier: NCT03728036; NCT03727919). These studies are designed and executed in adherence to the STROBE statements and were approved by the local Ethics Committee of the Antwerp University Hospital (Edegem, Belgium) in accordance with the declaration of Helsinki (main ethics committee protocol number: 18/25/305; Belgium trial registration number: B300201837010). The responsible ethics committees of all other involved clinical sites were asked for advice and additional approval before the study started.

### Participants

In total, this study will include a cohort of 60 patients after a first-ever hemispheric stroke of ischemic or hemorrhagic cause within, at most, 3 years of recruitment. This cohort will be recruited from the stroke units at the University Hospital Antwerp (Edegem, Antwerp, Belgium), the GZA Hospital campus St Augustinus (Wilrijk, Antwerp, Belgium) and the General Hospital Geel (Antwerp, Belgium). All cooperating hospitals are located in the larger Antwerp region in Flanders, Belgium. Stroke survivors will be screened and asked to participate as soon as possible and within the first 3 weeks after stroke onset. Only survivors who are, or will be admitted to one of the involved rehabilitation facilities (RevArte, Edegem, Antwerp, Belgium or the rehabilitation hospital Geel, Geel, Antwerp, Belgium) for inpatient treatment (eventually followed by outpatient treatment) are considered for inclusion, as the repeated measurements will be performed there. In addition, ten middle-aged (i.e., 45 to 65 years) healthy adults (gender equally distributed) with no known musculoskeletal or neurological injury or illness that may affect balance control will be recruited to serve as controls for the interpretation of posturographic measures of quiet stance balance control.

Before entry, an information brochure about the study's aim, content and potential risks, together with information about the investigators is provided to each prospective subject (and if adequate to her/his family). If the subject feels sufficiently informed and agrees to participate, an informed consent is signed and eligibility is determined according to the following criteria.

#### Inclusion Criteria

A first-ever, CT- or MRI-confirmed, supra-tentorial stroke in the anterior or middle cerebral arteria territory of ischemic or hemorrhagic cause;Impaired motor functions of the lower limb, defined as a score of > 0 on the NIHSS item 6 (i.e., at least “drift of the leg within 5 s without a fall”) within 3 days after stroke onset (or self-reported if data is missing), and a MI-LE score of ≤ 91 (i.e., at least “movement against resistance but weaker” in one item) at the moment of inclusion;Age between 18 and 90 years;Sufficient motivation to participate.

#### Exclusion Criteria

Dependent in daily life activities before stroke onset, defined as a pre-morbid Functional Ambulation Category score of <4 and a modified Rankin Scale score of >1;Having a preexisting orthopedic or neurological condition that affects motor functions of the lower limbs and/or standing balance control;Severe cognitive or communication deficits that may hinder informed consent and execution of the study;Not Dutch, German or English speaking prior to the stroke incident.

### Design

The current recovery study is a non-interventional observational study meaning that no systematic interventions are applied next to usual care. For the duration of inpatient rehabilitation, this consists of 30- to 60-min sessions of physical and occupational therapy each workday following local guidelines.

After eligible subjects are included within the first 3 weeks poststroke, serial measurements will be scheduled at 3, 5, 8, and 12 weeks poststroke. Clinical evaluations are performed by the same assessor for each participant to decrease the effect of inter-rater variability when measuring within-subject change. In total, two physical therapists are available for clinical testing who underwent a training period to standardize assessment procedures prior to the study start. As soon as subjects are able to stand independently barefoot over at least 30 seconds, bilateral posturography will be performed during a standardized quiet stance task. For this purpose, either two separate force-plates (Type OR 6-7, AMTI, MA, US; measurement frequency 1 kHz) arranged in a side-by-side configuration as part of a stationary movement analysis laboratory (*M*^2^*OCEAN*, University Hospital Antwerp, Edegem, Belgium) or a portable pressure-plate system (0.5 m footscan 3D, RS Scan, Belgium; measurement frequency 500 Hz) will be used. This provides the advantage of executing this study in multiple (clinical) settings to facilitate recruitment and continuous data acquisition. Importantly, repeated within-subject measurements are always performed with the same equipment and these measurements are performed by a trained physiotherapist who is educated in using the measuring instruments.

### Data Collection and Processing

During the uptake procedure, the participant's demographics including sex and age together with information about the stroke lesion in terms of type (i.e., infarct or bleeding) and side (i.e., left or right hemisphere affected) is collected. Length of stay in the rehabilitation hospital and discharge destination will be recorded throughout the study.

Before each balance assessment, the subject's body weight and length is measured. Next, the subject's bare feet will be positioned in parallel with a 8.4 cm heel-to-heel distance and in a 9° toe-out angle on the measuring plate (40). Manual support will be provided during standing up until the subject feels comfortable to stand independently. Now, the subject is instructed to maintain this position for 40 s with the arms alongside the trunk and the eyes open. They are asked to look straight ahead at a visual target at an approximately 2-meter distance. Subjects are encouraged to adopt a spontaneous, stable posture rather than standing as symmetric as possible. Three trials will be performed and if the subject got distracted, lost balance or moved the arms or head in a way that is not related to balance, the trial is excluded.

From each eligible trial, the first 10 s will be removed to prevent the influence of starting effects. Previously it was shown that 30 s quiet stance registration yield excellent test-retest reliability (43). Limb-specific COP trajectories will be calculated based on raw force components and low-pass filtered using a zero-lag, second-order Butterworth filter with a 10 Hz cutoff frequency. For the calculation of synchronization and contribution measures, these trajectories will be split into an anteroposterior (AP) and mediolateral (ML) signal based on the orientation of the feet by rotating the reference system. The COP underneath both feet combined will be used to estimate overall stance stability. For this purpose, we focus on velocity parameters as these are shown to have greatest reliability (44, 45) which has been confirmed for bilateral posturography in stroke survivors (46). These studies also show that usually two to three trials are sufficient to reach reliable data (45, 46) which is of relevance for this project since instability is pronounced early after stroke allowing to acquire only few standing attempts. All data processing (and parameter calculation, as documented below) will be done by using custom-made Matlab scripts (The MathWorks Inc., MA, USA).

### Outcomes

Poststroke recovery is a complex matter and the inconsistent use of terminology in the literature creates opportunities for confusion. Therefore, we first define the chosen outcome variables following the ICF framework (see Figure 1) and differentiate between dependent and independent variables for subsequent analyses.

**Figure 1 F1:**
[figure not shown]
ICF model. The upper panel provides an overview of ICF items that are required for (i.e., level of body functions, colored green) and dependent on (i.e., level of activities, colored yellow, and participation, colored red) standing balance control. The items that are directly assessed in the current study are highlight in bolt. In the lower panel metrics corresponding to these items of interest are provided. The color-coding indicates that metrics of quality of task performance and task accomplishment are both primarily situated on the level of activities, whereas the first indicates how movement execution functions (i.e., level of body functions) are assembled to execute a balance task. Contrary, task accomplishment means if a subjects is successful in maintaining standing balance, irrespective of the underlying control strategy, as a determinant of independence in daily life activities and participation (i.e., level of participation).

#### Independent Variables of Outcome

The main independent variables for modeling longitudinal associations with balance control measures (i.e., project B) are time-dependent, or dynamic, and situated on the ICF level of body functions (see Table 1). On this level, recovery means the restitution of rudimental functions of movement execution (19, 35), such as synergy-dependency and strength which we define as follows.

**Table 1 T1:** Measurements per assessment occasion.

**Domain/measure**	**Measurement occasions (time poststroke)**				
	**<3 weeks (i.e., inclusion)**	**3 weeks**	**5 weeks**	**8 weeks**	**12 weeks**
**Uptake procedure**					
Informed consent	X				
**Independent variables: Potential covariates/confounders**					
Demographics: Gender (m/f/x), Age (years)	X				
Lesion characteristics: Type (infarct/bleeding), Side (left/right hemisphere)	X				
Anthropometrics: Body Height (mm), Body Weight (kg)^*^	X	X^*^	X^*^	X^*^	X^*^
Other: Equipment (force-plates/pressure-plate)	X				
**Independent variables: Body functions level-Lower limb motor impairments**					
Fugl Meyer assessment–lower extremity		X	X	X	X
Motricity Index–lower extremity		X	X	X	X
**Dependent variables: Activity level-Quality of task performance**					
Between-limb synchronization		X	X	X	X
Dynamic control asymmetry		X	X	X	X
**Dependent variables: Activity level-Task accomplishment**					
Berg Balance Scale–standing unsupported item		X	X	X	X
Stance stability		X	X	X	X

*A scheme of the obtained metrics and items per assessment occasion is presented. Note, body weight (as marked with a ^*^) is the only potential additional covariate that is considered time-dependent and is therefore assessed at each follow-up occasion*.

##### Dynamic Variables

Although different definitions and constructs of muscle synergies exists in the literature (47), we refer to synergies as the clinical phenomenon of “pathological intra-limb synergies” meaning the loss of independent joint control leading to the emergence of stereotypical flexor and extensor movements (48) (i.e., ICF item b760 “Control of voluntary movement functions”). As such, muscle synergies are defined as an “increased co-activation between muscles in the paretic limb that can be elicited voluntarily” (48). Second, muscle strength is defined as the ability to produce a “maximum voluntary force or torque” through a muscle or muscle group contraction around a single joint (i.e., ICF item b730 “Muscle power functions”) (49). The following standardized clinical scales will be used to address these functions.

**Fugl Meyer motor assessment–lower extremity (FMA-LE)**: Muscle synergies will be assessed by means of scores on the FMA-LE, ranging from 0 (i.e., unable to move the limb or evoke tendon reflexes) to 34 points (i.e., able to selectively flex the knee and ankle joint in standing and normal reflexes). This scale has been reported to have excellent inter-rater [Pearson's *r* = 0.96 (50); ICC = 0.91, 0.97–1.0 95% CI (51)] and intra-rater reliability [ICC = 0.99, 0.91–1.0 95% CI (51)] when assessed in stroke survivors. Moreover, we use the standardization method of See et al. (52) to improve scoring consistency.**Motricity Index–lower extremity (MI-LE)**: Muscle strength in hip flexion, knee extension and ankle dorsiflexion direction will be assessed with the MI-LE. Active range of motion and force against manual resistance will be compared between both sides and evaluated with scores varying between 0 (i.e., no voluntary muscle contraction) and 33 points (i.e., full movement against gravity and equal strength) for each item. This scale has shown excellent intra-rater [ICC = 0.93, 0.84–0.97 95% CI (53); Spearman's rho = 0.87 (54)] and inter-rater reliability [Spearman's rho = 0.87 (54)] in stroke survivors.

##### Fixed Variables

Fixed, or time-dependent variables that are hypothesized to be potential confounders will be used as additional covariates. This includes the subject's age and gender at inclusion, as well as their Body Mass Index (BMI) (see Table 1). Body weight is serially assessed at each occasion and if significant fluctuations are seen over time, the BMI may be added as a dynamic variable. In addition, the stroke type and side will be added. Lastly, the used equipment for serial subject-specific measurements will be evaluated as a potential confounder.

#### Dependent Variables of Outcome

Dependent variables of outcome will be investigated in this study on the time course of recovery (i.e., project A) and longitudinal associations (i.e., project B). These outcomes are situated on the ICF level of activities where recovery comprises a general improvement in the ability to execute purposeful movements in a task context (19, 35). In the current study, the task of maintaining a quiet standing posture (i.e., ICF item d4154) will be evaluated which is defined as “the ability to control the body's center-of-mass relative to the base of support in fairly predictable and non-changing conditions” (55). For this purpose, we use and distinguish metrics addressing the quality of performance from those showing the mere accomplishment on this task.

##### Quality of Task Performance

Quality of task performance is “defined through a direct comparison of a patient's motor execution of a task […] to able-bodied control subjects” (35). This means that the closer the movement matches those seen in controls, the better the quality. With regard to standing balance, quality of performance is best reflected by measures that establish the (a-)symmetry between the most- and less-affected side considering that healthy balance control is characterized by equal output generated through the legs in the form of corrective COP movements (39, 56, 57). For this purpose, synchronization and contribution measures will be calculated that show how well both limbs act together (32, 39, 56) and are equally involved (31, 57) in maintaining standing balance. As COP in the ML direction is less meaningful for bipedal balance control (56), we focus on the sagittal plane.

**Between-limb synchronization:** Between-limb synchronization is a measure of the temporal structure and similarity between bilateral COP (39, 56). For this purpose, the mean position is subtracted from left and right AP COP trajectories and, next, a cross-correlation at zero-phase leg on a frame-by-frame basis is calculated. This measure therefore shows how well COP displacements are alike, or synchronized.**Dynamic control asymmetry (DCA)**: DCA is a symmetry index of the root mean square (RMS) of the AP COP velocities for each leg separately (31, 57). A score of zero indicates equal contribution of both legs to balance control and positive or negative values indicating a relatively larger involvement of the less- or most-affected leg, respectively. We use the following equation: Symmetry index: 2x (RMS COP AP velocity *less-affected*- RMS COP AP velocity *most-affected*) / (RMS COP AP velocity *less-affected* + RMS COP AP velocity *most-affected*).

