### Objectives

In the current manuscript, we describe an observational cohort study that aims to prospectively investigate the time course of recovery of quiet stance balance control in the first 12 weeks after a first-ever hemispheric stroke. The relatively low functional demands of this condition (as compared to perturbed stance or walking) enables us to describe the process of balance skill re-acquisition even in more-severely impaired subjects and in the time window of spontaneous neurological recovery. Simultaneously, we will clinically observe the time course of recovery of lower limb motor impairments to investigate longitudinal associations with this leg's contribution to balance control.

The pre-defined research questions and hypotheses are:

What is the time course of recovery in the first 12 weeks poststroke in terms of balance control (a-)symmetries and overall stability during quiet stance? (i.e., project A).

First, we hypothesize that improvements in balance control symmetries toward values seen in healthy controls, as assessed through bilateral posturography (i.e., between-limb synchronization and contribution measures of corrective COP movements), are restricted to the first 5 weeks poststroke. Second, we hypothesize that an improved ability to maintain a stable standing position following traditional posturographic measures of body sway (i.e., stance stability) may develop beyond the time window and up until 12 weeks poststroke. As such, these later changes are hypothesized to reflect compensatory body stabilization exerted through the less-affected leg.

How are improvements in muscle synergies and ankle strength of the most-affected leg longitudinally associated with this leg's contribution to quiet stance balance control in the first 12 weeks poststroke? (i.e., project B).

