First, we hypothesize that clinical improvements in muscle synergies (i.e., Fugl-Meyer Motor Assessment) and strength (i.e., Motricity Index) at the hemiplegic side are mainly seen within the first 5 weeks poststroke, in accordance with previous longitudinal studies investigating time-dependent change (20, 23). Second, we hypothesize to find within this time window longitudinal associations between recovery on these scales and improved between-limb symmetry in balance control. This means that clinically observed improvements in motor impairments relate over the first weeks to an improved ability of this leg to contribute to corrective COP movements while standing quietly.

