#### Statistical Analysis

##### Project A

In project A, we aim to investigate time-dependent changes in metrics of quiet stance balance control. To estimate how each parameter is changing as a function of time poststroke, we use a random coefficient analysis (or mixed model analysis) with “time” of measurements as the main fixed effect (JMP Pro, version 15). Additionally, “time” will be entered as an independent covariate in form of an subject-specific slope (i.e., the interaction term “participant^*^time”) to adjust for dependency of repeated observations. However, the greatest advantage of this method is its flexibility in dealing with missing values. The latter may result from subjects being unable to stand at first occasions, being unavailable due to hospital discharge or transfers, or by no longer corresponding to eligibility criteria for example due to a recurrent stroke or other sudden medical condition (potentially) affecting outcome variables. Moreover, the value on the addressed metric at 3 weeks poststroke will be added to account for inter-subjects variability.

In addition, fixed covariates that are hypothesized to be potential confounders will be entered in the model. This includes “gender,” “age” and “BMI” considering their influence on standing balance control. [i.e., females and elderly tend to show greater body sway (60) and obesity is associated with instability (61)]. Second, stroke “side” and “type” will be added, as right-sided lesions typically result in greater balance deficits (62) and subjects with hemorrhagic strokes may display delayed recovery (63). Lastly, “equipment” is added as a potential confounder considering technical variations in measuring instruments.

Statistical analysis of the difference in each measure of quiet stance balance control between subjects and healthy controls will be performed using the Mann-Whitney U test for each measuring system separately.

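### The Project A symmetry hypothesis and the comparison with controls rest on a signed DCA, which tracks the share between the legs and not the distance from symmetry

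*Protocol article*

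**What the plan says.** Under Quality of Task Performance, the Protocol article gives the index as DCA = 2(L − M)/(L + M). L and M are the RMS anteroposterior COP velocities of the less- and most-affected leg. It reads the index as follows: "A score of zero indicates equal contribution of both legs to balance control and positive or negative values indicating a relatively larger involvement", by the less-affected leg when positive and by the most-affected leg when negative. The same section characterises healthy control as equal output from the two legs and sets the standard for quality: "This means that the closer the movement matches those seen in controls, the better the quality".

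Under Objectives, the first Project A hypothesis concerns "improvements in balance control symmetries toward values seen in healthy controls", expected only in the first 5 weeks. The second Project B hypothesis looks for "longitudinal associations between recovery on these scales and improved between-limb symmetry in balance control". The sentence after it explains this as the most-affected leg becoming better able to contribute.

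Under Project A: "To estimate how each parameter is changing as a function of time poststroke, we use a random coefficient analysis", with time as the main fixed effect and a subject-specific slope. Each balance measure is also compared with healthy controls by a Mann-Whitney U test, separately for each measuring system. Project B takes DCA as the dependent variable. Neither section mentions an absolute value, a distance from the control value, or the handling of negative values.

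**The concern.** The best value of DCA lies inside its range, at zero, and asymmetry grows in both directions from it. Improvement toward control values is therefore a fall in distance from zero. A linear time coefficient on signed DCA estimates something else: the average shift of share from one leg to the other. The two agree while every patient stays above zero and separate once some do not.

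The first Project A hypothesis is at stake. With patients on both sides of zero, real gains in symmetry partly cancel in the mean slope. A group whose values centre on zero can look similar to controls in location while its members remain asymmetric. The comparison with controls has a further gap: the sign depends on which leg is most affected, and the article does not say how it is assigned in healthy adults.

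**Working it through.** **No planned figure to reproduce.** The sample size of 60 rests on recruitment and drop-out rates and a rule of 10 subjects per variable. No DCA effect size enters it.

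**Step 1: the formula on assumed velocities (L/M).**

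| L/M, before to after | DCA before | DCA after | Signed change | Change in asymmetry |
|---|---|---|---|---|
| 12/6 to 10/8 | 2(6)/18 = 0.667 | 2(2)/18 = 0.222 | −0.444 | −0.444 |
| 10/8 to 9/9 | 2(2)/18 = 0.222 | 0 | −0.222 | −0.222 |
| 8/10 to 9/9 | 2(−2)/18 = −0.222 | 0 | +0.222 | −0.222 |
| 10/9 to 9/10 | 2(1)/19 = 0.105 | 2(−1)/19 = −0.105 | −0.211 | 0 |

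In rows 2 and 3 both patients reach perfect symmetry, yet their mean signed change is (−0.222 + 0.222)/2 = 0. Their mean asymmetry falls by 0.222. Subject-specific slopes do not prevent this, because the fixed time effect is still the average of slopes of opposite sign.

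Swapping the leg labels turns 2(L − M)/(L + M) into its negative. Signed DCA in a control therefore depends on an arbitrary label, while |DCA| does not.

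**Step 2: size in closed form.** Assume DCA at week 3 is normal with mean μ and SD s, and write r = μ/s. The share below zero is Φ(−r). The mean absolute value is s·[√(2/π)·exp(−r²/2) + r(1 − 2Φ(−r))]. If every patient closes the same fraction of the distance to zero, the signed mean change divided by the mean change in asymmetry equals μ divided by that mean absolute value.

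| r | Share below zero | Mean absolute DCA, in SDs | Signed ÷ absolute gain |
|---|---|---|---|
| 0 | 50% | 0.798 | 0 |
| 0.25 | 40% | 0.823 | 0.30 |
| 0.5 | 31% | 0.896 | 0.56 |
| 1 | 16% | 1.167 | 0.86 |
| 1.5 | 7% | 1.559 | 0.96 |
| 2 | 2% | 2.017 | 0.99 |

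The first row also shows that a group with mean exactly zero keeps a mean |DCA| of 0.798 s, which is 0.24 for s = 0.3 and 0.32 for s = 0.4.

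**Step 3: simulation.** Taken from the article: 60 × 0.85 = 51 patients after 15% drop-out; weeks 3, 5, 8 and 12; 10 controls; two-sided 0.05. Assumed: SD 0.4, residual SD 0.1, controls centred on zero with SD 0.1, and every patient truly halving the distance to zero between weeks 3 and 12. There were 2,000 runs, with per-subject slopes tested by a t-test.

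| Mean DCA (share below zero) | Change, signed | Change, absolute | Slope test rejects, signed / absolute | Week-12 Mann-Whitney rejects, signed / absolute |
|---|---|---|---|---|
| 0 (50%) | 0.00 | −0.15 | 5% / 100% | 1% / 69% |
| 0.2 (31%) | −0.10 | −0.17 | 83% / 100% | 30% / 81% |
| 0.4 (16%) | −0.20 | −0.23 | 100% / 100% | 94% / 96% |
| 0.6 (7%) | −0.30 | −0.31 | 100% / 100% | 100% / 100% |
| 0.8 (2%) | −0.40 | −0.40 | 100% / 100% | 100% / 100% |

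The simulation has complete data, pools the two measuring systems and simplifies the mixed model. The contrast between signed and absolute results is what counts, not the level of power. The absolute change is slightly below its closed-form value (at mean 0.2: 0.5 × 0.896 × 0.4 = 0.179 against 0.17) because noise near zero inflates |DCA|.

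**The case against.** The strongest reply is that signed DCA is the right quantity for much of what the study asks. The second objective and the Project B question concern the most-affected leg's relative contribution, and the Project B hypothesis is explained in those terms. That is monotone in signed DCA, and the sign shows which leg dominates, which bears on separating restitution from compensation. This stands: the Project B outcome is not misdefined.

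Second, the background points to mostly positive values. The Introduction and Discussion sections on mechanisms describe disproportionate reliance on the less-affected leg, and considerable asymmetry, even in patients with near-normal clinical scores. This also stands and limits the likely size. A reader might infer from the MI-LE entry limit of 91 that the effect must be large in mildly impaired patients. The documents do not support that, and these passages point the other way.

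Third, a reader might infer that the plan counts moves past zero as improvement and a rise from a negative value as worsening. The article says neither. It explains what each sign means, asks in Project B only whether impairment scores relate to changes in DCA, and tests two-sided. It also has no rule that a group mean of zero shows restored symmetry.

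Fourth, between-limb synchronization is a second quality measure without this sign problem. That is true, but DCA is the stated measure of equal involvement of the legs, and the hypothesis covers both measures.

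None of these replies supplies a measure of distance from symmetry for the Project A hypothesis or a sign for the controls.

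**Conclusion.** The concern holds as a mismatch between the Project A symmetry hypothesis, with its control comparison, and the signed outcome used for both. The mean slope or group location of signed DCA cannot by itself show that symmetry improved or was restored. This follows from the article's own formula and its own definition of quality.

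The size is unknown, because no DCA distribution is given. Under the normal, proportional-recovery assumptions above, the distortion is negligible when about 7% of patients or fewer are below zero. It is material at about 30% or more, where the signed change misses roughly 40% of the gain in symmetry (1 − 0.56 = 0.44 in closed form; 1 − 0.10/0.17 = 0.41 in the simulation). The background makes the lower end more plausible without excluding the upper. The undefined sign in controls does not depend on these assumptions.

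**What to change.** - For the Project A symmetry hypothesis and the comparison with controls, also analyse |DCA|, computed per occasion after averaging trials, with the same random coefficient model and Mann-Whitney test. Base statements about improved or restored symmetry on that result.
- Report the number of patients with DCA below zero at each visit. This alone shows whether the issue matters in this cohort.
- Keep signed DCA as the measure of the most-affected leg's relative contribution and as the Project B dependent variable, and word Project B results as relative contribution. A hybrid-model run on |DCA| is optional.

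The cost is one derived variable from data already collected, one further time model and one further set of control comparisons. The drawback is that |DCA| is bounded at zero, skewed and slightly inflated by noise near zero. It should therefore stand next to signed DCA and not replace it.
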